**Figure 1 figure1:**
[figure not shown]
Techniques and applications influence perceived susceptibility in the current trial. The main determinant behind perceived susceptibility is a lack of knowledge regarding prescribed medications and the influence on risk reduction.

**Figure 2 figure2:**
[figure not shown]
Techniques and applications influence perceived severity in the current trial. The main determinant behind perceived severity is patients’ beliefs, perception and management of their illness (awareness, outcome expectations).

**Figure 3 figure3:**
[figure not shown]
Techniques and applications influence perceived benefits in the current trial. The main determinant behind perceived benefits is patients' beliefs, perceptions, and management of their illness (awareness).

**Figure 4 figure4:**
[figure not shown]
Techniques and applications influence perceived barriers, cue to action, and self-efficacy in the current trial. The main determinant behind perceived barriers is skills and self-efficacy.

## Results

### Primary Outcome

The primary outcome of our study is adherence to the CVD medication (classified by the Anatomic Therapeutic Chemical classification system) measured with a dedicated calculation of refill data of the used plated aggregation inhibitors and lipid modifying agents obtained from patient’s pharmacy.

Refill records of computerized pharmacy systems will be collected from 3 years prior to a patient’s cardiovascular event through up to 3 years after the study follow‐up period. Prescription records include the names of all of the dispensed drugs, prescribed daily dose, quantity dispensed at each pharmacy fill, and the dates of the prescription fills. Adherence will be calculated for the CVD medications as the theoretical duration divided by the period between the start date and the date of the last prescription filled. The theoretical duration will be calculated by dividing the number of units dispensed by the prescribed daily dose [25].

Patients with an adherence level of at least 80% will be classified as adherent, and patients with an adherence level less than 80% will be classified as nonadherent. Secondary prevention studies showed that patients with an adherence of less than 80% have an increased risk of death [26].

Refill adherence rates have been used extensively for the assessment of drug acquisition and dispensing. Compared with electronic monitoring, refill data provide researchers with a relatively simple method for investigating exposure to medication in large populations [27-29]. Moreover, this method is suitable for investigating long‐term persistence to treatment and gaps in medication supply [30].

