**Results:**

Primary outcome is adherence to treatment calculated by refill data. Secondary outcomes include the Beliefs about Medication Questionnaire and the Modified Morisky Scale. Patients are followed for one year. Results are expected by 2015.

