### Recruitment

All cardiovascular patients who receive the regular cardiovascular preventive care will be asked to participate by a nurse when they arrive at the outpatient clinic for their screening consult. Patients will receive a letter explaining the study, documenting their ability to withdraw at any time without explanation, and confirming that their medical care will in no way be influenced by their decision regarding participation. At a minimum of 24 hours later, written consent will be sought by a research assistant prior to the patient entering the study.

We chose to include all cardiovascular patients in our study rather than only nonadhering patients as done in many other studies [6,9,34]. The reason is that we plan to do a 3-year follow-up and want to be able to see how adherence develops over time for initial adherers and nonadherers alike.

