### Statistical Methods

The data will be analyzed based on the intention‐to‐treat principle and evaluated using SPSS, with descriptive statistics (mean, median, SD, and interquartile range) being determined for all variables. The data will be presented in quantitative format (eg, biometrics, laboratory results, blood pressure, lifestyle scores, adherence score on the basis of refill data, and the MMS) and in descriptions of observed effects (eg, change in BMQ, determinants for adherence, evaluation of the use of iVAZ, and appreciation of nurse intervention).

To evaluate the difference between the groups, an analysis of variance test will be performed on the outcome measures for the three patient groups. The independent variable will be the three intervention groups. The dependent variable is medication adherence measured with the dedicated calculation of refill data. Specifically, we will compare the difference between the first and last time-point between groups for the primary and secondary outcomes measures. For the intervention groups II and III, we will also compare the outcomes of the clinical data at 16 and 28 weeks. To correct for multiple comparison, a Duncan’s multiple range test will be performed. Furthermore, we will perform a receiver operating characteristic (ROC) curve analysis to compare the outcome of the screening instruments (MMS and BMQ) with the pharmacy refill dates. In the ROC curve plot, specificity of the questionnaire is on the x-axis and sensitivity of the question is on the y-axis.

Plausible relations between parameters of cardiovascular risk factors, motivation to change, socioeconomic class, and parameters of adherence (calculated refill score and BMQ and MMS scores) will be tested in a univariate manner. Individual parameters will be tested for normality using the Kolomogorov-Smirnov test in order to select adequate univariate tests. Multiple logistic regression analysis will be performed to assess the relative importance of selected parameters for the likelihood of low adherence, as defined by the refill data algorithm. In all analyses, potential confounders will be included if they independently changed the beta coefficient for dedicated calculation of refill data by at least 5% or when consensus about inclusion existed within the team of researchers supported by clinical evidence from literature.

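### The primary refill ratio runs from an undefined start date to the last fill, with neither end tied to randomisation or month 12, so supply from before the trial can enter it and dilute the effect

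*Protocol article*

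**What the plan says.** The Primary Outcome section makes two separate statements. The first is about data collection: refill records "will be collected from 3 years prior to a patient’s cardiovascular event through up to 3 years after the study" follow-up. The second is the calculation: adherence is "the theoretical duration divided by the period between the start date and the date of the last prescription filled", where theoretical duration is units dispensed over prescribed daily dose. The section does not define the start date and does not mention randomisation. The same ratio is then cut at 80% to classify patients as adherent or not.

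Four other sections bear on the time frame:

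- The Abstract (Results) says "Patients are followed for one year".
- Secondary Outcomes times its measurements just before inclusion and one year after it. The primary outcome has no matching sentence.
- Recruitment says "we plan to do a 3-year follow-up and want to be able to see how adherence develops over time".
- Statistical Methods says "The dependent variable is medication adherence measured with the dedicated calculation of refill data", and that "we will compare the difference between the first and last time-point between groups for the primary and secondary outcomes measures". It gives no interval over which either refill value is computed.

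**The concern.** The trial asks whether the intervention improves adherence, and the intervention can act only after randomisation. A refill ratio is an average over an interval, so its meaning depends on where the interval opens and closes. Here the opening date could be the first fill on record, the start of therapy, the cardiovascular event or randomisation. The closing date is each patient's last fill, which may fall before or after month 12.

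If the interval opens before randomisation, the ratio mixes the trial year with time that the intervention could not affect. The mix differs between patients according to how long each had been on the drug. Randomisation keeps the groups comparable, so the expected result is an effect shrunk towards zero, not a spurious one. The loss is in power and in what the estimate means. A choice left open in the primary outcome could also be made after the data have been seen.

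**Working it through.** **Inputs from the article**

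- Sample Size: adherence 65% at the start, steps of 10 points, SD 30, two-sided alpha .05, power 80%, 200 per group.
- Eligibility Criteria: diagnosis within the last 6 months.
- Primary Outcome: records reach back 3 years before the event.
- Abstract: one year of follow-up.

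**The plan's own figure.** For two means, n per group = 2 × (1.960 + 0.842)² × 30² / 10² = 141.3, so 142. The stated 200 is not reproduced by these inputs, but it exceeds the requirement. With 200 per group the standard error of a difference is 30 × √(2/200) = 3.0 points. Power for 10 points is Φ(10/3.0 − 1.96) = Φ(1.37), about 91%. That is the reference value here. The gap between 142 and 200 is a separate matter.

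**Dilution.** Let a patient have L years on drug before randomisation at adherence a, then one trial year at a + 10. Over the whole interval the ratio is

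(L × a + 1 × (a + 10)) / (L + 1) = a + 10/(L + 1).

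The between-group effect is therefore 10/(L + 1).

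**Range of L**

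- L = 0: the start date is randomisation.
- L = 0.5: the drug was started at the event and the patient entered at the 6-month limit, taking event and diagnosis as the same date.
- L = 3.5: the drug was already in use 3 years before the event and the patient entered at the 6-month limit. This is about the longest history that the records can show.

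| L (years) | Effect (points) | Power, 200 per group, SD 30 |
|---|---|---|
| 0 | 10/1 = 10 | about 91% |
| 0.5 | 10/1.5 = 6.7 | Φ(6.67/3.0 − 1.96) = Φ(0.26), about 60% |
| 3.5 | 10/4.5 = 2.2 | Φ(2.22/3.0 − 1.96) = Φ(−1.22), about 11% |

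Each row treats all patients as having that L. A real sample would be a mixture, and the article does not give the shares.

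**Does the change from first to last measurement remove the dilution?** It depends on the interval behind the last value, which is not given.

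- If the last value is cumulative from the start of the drug and the first is the ratio up to randomisation, the change is (a + 10/(L + 1)) − a = 10/(L + 1). The dilution remains.
- If the last value covers only the trial year, the change is (a + 10) − a = 10. There is none.

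The formula in Primary Outcome fits the first case if the start date is the start of the drug. It fits the second only if the start date is randomisation.

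**The case against.** The strongest reply is that the long span describes what is collected, not what is computed, and this is correct. A reader might infer that everything from 3 years before the event to 3 years after follow-up goes into one ratio, so that dilution is built into the plan. The documents do not say so, and three passages point the other way:

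- Sample Size expects a baseline adherence, which refill data can supply only from earlier records.
- Statistical Methods compares a first with a last value.
- Recruitment gives the later records their own purpose, since "we plan to do a 3-year follow-up".

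A reader might also infer that patients enrolled early get longer windows than those enrolled late. That needs a common calendar cut-off, and none is stated. Pooling the three later years with the trial year is likewise not stated, and its effect would depend on whether the gain persists. One-year follow-up and a longer later look do not conflict.

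The power figures also rest on assumptions. SD is held at 30, although averaging over a longer interval may well reduce it. L = 3.5 applies only to patients long on treatment before the event. No single expected power loss can be derived.

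Finally, index dates are often left to a full protocol or analysis plan, and the article cites a source for the calculation that is not at hand. This carries some weight but does not dispose of the point. The article does more than leave a detail out: it states a working formula whose end is the last fill, which is not a one-year window, and whose wording admits supply from outside the trial year.

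**Conclusion.** The point holds as a badly fixed outcome window. Dilution is a conditional consequence, not a stated feature of the plan. Neither end of the primary ratio is anchored to randomisation or month 12, and the planned change from first to last measurement does not supply the missing intervals.

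Depending on how one undefined term is read, a 10-point gain in the trial year appears as anything from 10 points down to about 2.2, and power for one 10-point step runs from about 91% to about 11%. The range assumes 200 per group, SD 30 throughout, equal adherence in all groups before randomisation, and a common L within each scenario. Where the trial falls within it cannot be told from the article. Because this is the primary outcome, it should be settled before refill data are compared between groups.

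**What to change.** In Primary Outcome, define the primary measure as refill adherence in a fixed window that opens at randomisation and closes at day 365 for every patient, counting supply on hand at randomisation. Use refills from before randomisation only as a baseline value, where they exist, and state the interval for that value. Report refills after year 1 as a separate long-term outcome at one fixed horizon for all patients. In Statistical Methods, name these intervals as the two values being compared.

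The cost is small: no new data, visits or patients, because fill dates, quantities and daily doses are already collected. The extra work is computing the supply carried in at randomisation. Closing the window at day 365 also means that time after an early last fill stays in the denominator. This differs from the present formula and should be stated openly.

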## Introduction

### Background and Rationale

According to the World Health Organization, almost 50% of all chronic patients do not adhere to their prescribed drug regimen [1]. This is also true for cardiovascular diseases (CVD); only 60% of all cardiovascular patients adhere to their cardiovascular medications (eg, statins, antihypertensives, antithrombotic agents) [2]. This prevalence is similar across all individual CVD medications and occurred in patient who take these medications for primary and secondary prevention of CVD [2]. These figures are startling given that poor adherence results in an increased risk of death in cardiovascular patients [3-5].

Current methods for improving adherence are mostly complex and have limited effectiveness; simple interventions that are easy to implement in daily practice are preferred [6]. Evidence suggests that interventions should be based on the patients’ perspective [7], target patients’ capacity and practical barriers, and address their beliefs and perceptions regarding illness and medication [8,9]. In CVD, life-long adherence is important, and interventions should improve patients’ intentions to take medication as well as solve emergent practical barriers.

These principles were used in the development of the current trial. Specifically, the intervention is based on the health belief model (HBM) [10,11], tailored for the specific purpose of this trial. HBM provides a useful framework for designing behavior change strategies [12]. It is based on the understanding that a person will take health‐related action (eg, being adherent to cardiovascular medication) given four main factors. The first two factors are perceived susceptibility and perceived severity: understanding of the high personal risk and seriousness of a condition (eg, because of the cardiovascular event in the past I am at greater risk for another cardiovascular event). The third factor is perceived benefit, or a belief that a negative health condition can be avoided (eg, being adherent to the cardiovascular medication can help to prevent another cardiovascular event). The last factor is perceived barriers. Cue to action and self‐efficacy and the belief in the ability to successfully undertake the recommended health action (eg, I know how to take my medication on a daily basis) [12,13].

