#### Usual Care (Groups I, II, and III)

All new CVD patients receive the hospital‐wide screening program according to the Dutch guidelines [14] (based on the European guidelines [15]). The screening assesses cardiovascular risk factors in all patients with CVD. It screens for lifestyle risk factors, blood lipid levels, blood pressure, waist circumference, body mass index, blood glucose levels, and a family history of CVDs. Lifestyle is evaluated through a questionnaire which is a compilation of existing validated questionnaires regarding demographic data, smoking, alcohol use, physical activity, and eating habits. For each of these lifestyle issues, the patient’s motivation to change is evaluated [16]. Adherence is measured by the Modified Morisky Scale (MMS) [17] and the Beliefs about Medication Questionnaire (BMQ) [18]. Medication use will be monitored. If necessary and if the patients agree they attend consultations with a nurse based on motivational interviewing to help them lose weight, stop using alcohol, or stop smoking.

According to European guidelines [15], all patients with established CVDs (this means all participants of this trial) should have antiplatelet therapy (eg, aspirin or clopidrogel) and a lipid lowering drug (eg, simvastatin or atorvastatin). The use of antihypertensive drugs is dependent on the systolic blood pressure. Except for the specific additions for the study, all participating and nonparticipating patients receive the same regular preventive cardiovascular care including monitoring of medication use. All patients receive regular vascular care from their medical specialist.

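### The primary refill-adherence formula ends its denominator at the last fill, so permanent stopping goes uncounted and a prompt refiller who then stops is scored as adherent

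*Protocol article*

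**What the plan says.** The Primary Outcome section of the Protocol article gives the formula outright. Adherence is "the theoretical duration divided by the period between the start date and the date of the last prescription filled", and for the numerator: "The theoretical duration will be calculated by dividing the number of units dispensed by the prescribed daily dose". It does not say whether the supply handed out at the final fill belongs in the numerator. The score is then dichotomised: "Patients with an adherence level of at least 80% will be classified as adherent". The Statistical Methods section makes this refill measure the dependent variable of the main analysis of variance.

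The measure is applied to platelet inhibitors and lipid-modifying drugs. Under usual care, every participant "should have antiplatelet therapy (eg, aspirin or clopidrogel) and a lipid lowering drug". The abstract gives the follow-up: "Patients are followed for one year".

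Two statements show what the measure is meant to capture. The Background says "In CVD, life-long adherence is important". The Primary Outcome section says that refill data suit the study of long-term "persistence to treatment and gaps in medication supply". The article defines no separate persistence outcome.

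**The concern.** For a patient who stops for good, the clock stops at the last visit to the pharmacy. However long the drug-free period that follows, it adds nothing to the denominator, so the most complete form of nonadherence is not counted. A patient who continues with late refills does accumulate denominator time and is marked down for it.

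This is the only primary outcome, and the drugs are meant to be taken for life. If the website or the consultations work partly by keeping patients on treatment, the primary analysis is poorly placed to see that part of the effect. The formula also conflicts with the article's own claim that the method is suited to persistence and supply gaps: with this denominator, a final gap cannot register.

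**Working it through.** **Inputs.** From the article: the formula, the 80% cut, one year of follow-up, and the planned 10-point step (65% to 75% to 85%, SD 30%). Assumed, because the article gives no figures: 90-day fills, a 365-day year, and the stopping rates and refill delays below.

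**The plan's own figure.** The article contains no worked adherence score to reproduce. The one related figure is 200 per group. A two-group comparison of 10 points with SD 30, 80% power and two-sided alpha .05 needs 142 per group, and 200 would give 91.5% power, so 200 does not follow from the stated inputs alone. Nothing below depends on it.

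**Step 1: worked refill histories.** Stated score = days supplied / (first fill to last fill). Fixed-year score = days supplied up to day 365 / 365.

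| Refill history (90-day fills) | Stated, last supply excluded | Stated, last supply included | Fixed year |
|---|---|---|---|
| Days 0, 90, then stops | 90/90 = 100% | 180/90 = 200% | 180/365 = 49% |
| Days 0, 90, 180, then stops | 180/180 = 100% | 270/180 = 150% | 270/365 = 74% |
| Days 0, 130, then stops | 90/130 = 69% | 180/130 = 138% | 180/365 = 49% |
| Days 0, 120, 240, 360 (continues, late) | 270/360 = 75% | 360/360 = 100% | 275/365 = 75% |
| Day 0 only | 0/0, undefined | 90/0, undefined | 90/365 = 25% |

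With the last supply excluded, the patient who stops after two prompt fills is adherent (100%) and the patient who takes the drug all year with gaps is not (75%). Coverage of the year runs the other way, 49% against 75%. With the last supply included, both pass 80%, and the stopper still has the higher uncapped score.

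**Step 2: what a reduction in stopping looks like.** Simulation of 20,000 patients per scenario. Each patient's typical refill delay is drawn around 10 days (SD 20), single delays vary around it (SD 10), and negative delays are set to zero. Stopping times are uniform over days 30 to 300. The share who stop falls from 30% to 10%, with delays unchanged.

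| Measure | 30% stop | 10% stop | Change in mean |
|---|---|---|---|
| Fixed year, mean | 77.1% | 84.5% | +7.4 |
| Stated, last supply excluded, mean | 87.0% | 86.7% | -0.3 |
| Stated, last supply included, uncapped, mean | 125.7% | 119.4% | -6.3 |
| Stated, last supply included, capped at 100%, mean | 99.8% | 99.7% | -0.1 |

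The share at or above 80% rises from 53.9% to 68.6% in the fixed year. Under the stated formula with the last supply excluded it goes from 73.8% to 73.0%. Patients without a defined score: (20,000 - 18,288)/20,000 = 8.6% in the first scenario and (20,000 - 19,421)/20,000 = 2.9% in the second.

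**Step 3: if the patients kept on treatment refill late.** With the last supply excluded and an assumed typical delay of 30 to 60 days among retained patients, the stated mean falls by 2.3 to 5.5 points and the share at or above 80% falls by about 7 to 15 points. The fixed-year mean rises by 5.6 to 3.0 points.

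**Step 4: do the long records repair it?** No. Pharmacy data run up to 3 years beyond follow-up. They reveal a temporary gap if the patient later refills, but the last fill of someone who has stopped for good does not move.

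**The case against.** The best defence is that a denominator ending at the last fill measures how well patients take a drug while they are on it, and does not penalise a stop ordered by a prescriber. That is a legitimate quantity. It is only half of what the article sets out to capture, however, and the other half, persistence, has no outcome of its own.

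It can also be said that the article condenses a fuller protocol and cites a source for the calculation. Handling of a single fill, a cap at 100% and the last supply could well be settled there, and their absence is not criticised here. The denominator is different: it is stated, and the result follows from it.

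Several stronger readings are tempting, and the article does not support them:

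- *Every patient who stops is scored as adherent.* No. With the last supply excluded, long gaps before stopping can still put the score below 80% (69% for fills on days 0 and 130).
- *The 80% classification is meaningless.* No. With the last supply excluded, gaps between fills still count. The intervention also targets practical barriers and unintentional nonadherence, which such gaps can show.
- *The formula reverses the effect.* Only if the last supply is counted without a cap, or if retained patients refill late. The planning mean of 65% argues against the first reading, which gave means well above 100% in the simulated scenarios.
- *The effect is diluted by years of earlier data.* The article says "Refill records of computerized pharmacy systems will be collected from 3 years prior" and does not tie the start date to randomisation. But Statistical Methods compares the first and last time-points, which points to separate periods. Nothing says that the years are pooled into one ratio.

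The simulated sizes are also not anchored in the article: it gives no stopping rate, and group III is planned to differ from control by 20 points, not 10.

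**Conclusion.** The point holds. The stated denominator omits all time after the last fill, so discontinuation is invisible and a patient who refills reasonably on time before stopping is classed as adherent. This follows from the formula; the 100% (or 200%) against 49% example adds only the assumption of 90-day fills. The 80% classification is therefore unreliable.

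An effect that works by preventing stopping is largely missed. Under the assumptions shown, a 7.4-point gain in days covered, against a planned step of 10 points, appears as -0.3 points with the last supply excluded. The direction of this loss is a property of the formula; its size depends on stopping rates, fill lengths and delays that the article does not give. Reversal is possible under the two conditions named above, but should not be presented as the expected result. Because this is the sole primary outcome, it should be corrected before the data are analysed.

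**What to change.** Define the primary outcome as the proportion of days covered over a fixed window, from randomisation to one year and identical in all three arms, for the platelet inhibitors and lipid-modifying drugs that the patient is prescribed.

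- Carry in supply on hand at randomisation and cap the score at 100%.
- Count days after the last supply runs out as uncovered.
- End the window early only for death or a documented discontinuation ordered by a prescriber, so that such a stop, or a drug never prescribed, is not scored as nonadherence.
- Patients with a single fill, and patients prescribed a drug but with no fills, then have a defined score.
- Calculate any baseline score in its own window before randomisation.
- Reword the persistence claim to match the measure adopted.

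The cost is revised wording and a new program on the same pharmacy records, with no extra data collection. Reported adherence levels will look less favourable than under the present formula.

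### The primary adherence score stops counting at each patient's last fill, so permanent discontinuation during the trial year is not scored as nonadherence

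*Protocol article*

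**What the plan says.** The Primary Outcome section defines the score as theoretical duration "divided by the period between the start date and the date of the last prescription filled". On the numerator it says: "The theoretical duration will be calculated by dividing the number of units dispensed by the prescribed daily dose". It states no exclusion of the final fill's units, no cap, no rule for a patient who discontinues and no rule for a patient with a single fill. The start date and the scored window are not defined further.

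The score is then dichotomised: "Patients with an adherence level of at least 80% will be classified as adherent". Under Statistical Methods the refill score is the dependent variable of the analysis of variance, and "we will compare the difference between the first and last time-point between groups for the primary and secondary outcomes measures". The same section provides multiple imputation for missing observations and does not mention stopping treatment. The abstract gives the follow-up: "Patients are followed for one year". No other section adds time after the last fill back into the denominator.

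**The concern.** The denominator ends on a date that the patient's own behaviour sets. If a patient refills for some months and then stops for good, the untreated months drop out of the score. Observation is cut off by one of the events the intervention is meant to prevent: the background section argues that "In CVD, life-long adherence is important", and the Discussion names intentional nonadherence as a target.

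An intervention that works by keeping patients on treatment could then show little or no effect on the primary outcome. If the final supply is counted, an arm with more early stoppers could even gain score. Imputation does not help, because a patient who stopped after two or more fills has a computable score and is not missing.

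**Working it through.** The protocol gives no worked score to reproduce, so the check applies its formula to simple refill patterns.

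**Inputs.** From the protocol: the formula and the 80% cut-off (Primary Outcome), the 65% starting adherence and the 10-point planned step between adjacent groups (Sample Size), and one year of follow-up (abstract). Assumed: fill lengths of 30 or 90 days and equal spacing before stopping.

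**Formula.** Let each fill hold S days of supply, let a be the refill rate before stopping (spacing S/a), and let k be the number of fills. The last fill falls (k−1)·S/a days after the first.

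- As written: kS ÷ [(k−1)S/a] = a·k/(k−1). Time after the last fill is absent, and the value falls as k rises.
- With the last fill's units left out: (k−1)S ÷ [(k−1)S/a] = a, whatever the stopping date.
- With a fixed year: kS/365, capped at 1.
- With k = 1 the denominator as written is 0 and the score is undefined.

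**Results.**

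| Pattern (fill length assumed) | As written | Last supply excluded | Fixed 365 days |
|---|---|---|---|
| 90-day, a = 1, stops after 2 fills | 180/90 = 200% | 100% | 180/365 = 49% |
| 90-day, a = 1, stops after 3 fills | 270/180 = 150% | 100% | 270/365 = 74% |
| 30-day, a = 0.65, stops after 5 fills (last on about day 185) | 0.65 × 5/4 = 81% | 65% | 150/365 = 41% |
| 30-day, a = 0.65, refills all year (8 fills, last on about day 323) | 0.65 × 8/7 = 74% | 65% | 240/365 = 66% |

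In the last two rows, the patient who stops about halfway is classed adherent, while the patient who refills at the same rate all year is classed nonadherent.

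**Stop and restart.** On 90-day fills on days 0, 90 and 360, the score as written is 270/360 = 75%. The gap is seen because a later fill closes it.

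**Longer window.** If the start date lies well before the trial, k is larger and the inflation smaller. Four years of 90-day fills at a = 0.65 gives 11 fills and 0.65 × 11/10 = 71.5%. The direction is unchanged.

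**Between arms (illustration only).** Assume 90-day fills, on-treatment adherence with mean 85% and SD 10 points, stopping times uniform over the year, and 30% stopping in one arm against 10% in another. Simulated mean coverage is about 77% against 83%, or 6 points in favour of the better-retained arm. The ratio as written averages about 121% against 116% among patients with a score, or 5 points the other way. With the last supply excluded, both arms average about 85%. About 9% and 3% of the two arms have one fill and no score. With mean 65%, SD 20 points and 30-day fills, the wrong-sign difference shrinks to about 3 points.

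**The case against.** The strongest reply is that the reversal depends on how the last fill is handled. The text does not say in so many words that its units stay in the numerator, and it cites a source for the method that is not at hand. If the last supply is left out, early stopping earns no bonus. This stands as a limit on the reversal. It does not rescue the score, because the stopper then scores exactly the same as the patient who continued.

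A reader might also infer stronger things that the protocol does not support:

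- *That stopping never counts.* A stop followed by a refill is scored as a gap. Records run to 3 years after follow-up and the last fill is not tied to the trial year, so a late restart could also bring a gap into the score.
- *That the earliest stoppers score highest.* A one-fill patient has no score at all.
- *That nearly everyone would be classed adherent because of stopping.* Under the 90-day illustration almost all scored patients pass 80%, but this is already so with no stopping. It comes from counting the last supply in everyone.
- *That the trial will show the wrong sign.* This needs unequal stopping between arms. The protocol gives no stopping rates, and the illustration compares end scores whereas the plan compares change.
- *That the section contradicts itself* by saying refill data suit the study of "persistence to treatment and gaps in medication supply". That sentence describes refill data in general and makes no claim about this ratio.

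Finally, counting from randomisation has its own difficulties. Patients were diagnosed up to 6 months earlier and may hold supply already, and the change comparison needs a baseline score on the same basis. Both objections are sound, and the fix has to meet them.

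**Conclusion.** The outcome definition is wrong as written. Permanent discontinuation after the last fill does not enter the primary score, and this follows from the formula alone, with no assumption about fill lengths or stopping rates.

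On the literal reading, with all dispensed units counted, the score also rises the earlier a patient stops, among patients with at least two fills and equal refill spacing. The size depends on the assumed fill length: 200% or 150% against 49% or 74% coverage for on-time 90-day fills, and 81% against 74% across the 80% cut-off at the protocol's 65% rate with 30-day fills. Excluding the last supply removes the reversal and leaves a score blind to stopping.

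A bias between arms is possible but not established. In the 30% against 10% illustration, the gap between true coverage and the literal ratio is about 6 + 5 = 11 points, comparable to the planned 10-point step, but only under those assumed rates. Because the rule governs the primary outcome and is cheap to change, it should be corrected before analysis.

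**What to change.** Redefine the primary score as days covered by dispensed supply, divided by a common window from randomisation to day 365 (or death), capped at 100%. State that:

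- supply already in hand at randomisation is credited;
- days after supply ran out count as uncovered;
- patients with a single fill are included;
- a switch within the drug class counts as continued supply.

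Compute the baseline score on the same fixed-window basis from the pre-randomisation records, so that the change comparison in Statistical Methods is like with like. State the length of that baseline window. Report the share of patients with no supply at day 365 by arm beside the primary result.

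The cost is wording in the outcome definition and a changed calculation. Fill dates, quantities and prescribed daily doses are already collected, from before the cardiovascular event to well beyond one year. The downsides are that mean adherence will look lower than under the current ratio, and that stops ordered by a physician count as uncovered unless the records identify them.
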